### Registration and Consent Procedure

Participants can register online and will need to provide only minimal personal data, including their email addresses, phone numbers (only to get in contact with if follow-up questionnaires are not filled out), and some basic demographical data (age, gender, and level of education).

Before registration, each participant will be informed online about the study, specifically provided information about the following:

Purpose, background, and an overview of the studyInclusion and exclusion criteria (Tables 1 and 2)The difference between the three treatment arms (but no details about how the two active treatment arms differ) and their one in three chance of being allocated to each one of these three armsFinancial aspects (no participation fee, compensation for participation)Potential risks of participation and when to contact their general practitioner or, alternatively, a professional they can select from a medical advisory and emergency list that will be accessible at all times merely by clicking on emergency iconThe inability of CANreduce to replace face-to-face therapy for problematic cannabis use or abuseThe voluntary nature of participation and their right to withdraw from the study at any time without consequences, except for the loss of further compensationConfidentiality and data protection (anonymity is ensured by not recording real names or postal addresses and by deleting email addresses and phone numbers before statistical analysis and data archiving)The approval given by the ethics committee of the Canton Zurich after the committee had reviewed the study

Informed consent will be accepted once participants have activated several check boxes restating important study points and have submitted their consent by clicking a submission button.

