**Figure 1 figure1:**
[figure not shown]
Trial flowchart.

**Table 1 table1:** Inclusion criteria and underlying rationale.

Inclusion criteria	Reasoning
Informed consent via the Web form	To ensure knowledge of procedures and the declaration of consent
Minimal age of 18 years	To ensure a minimum age of participation
Cannabis use at least once weekly over the last 30 days	To include participants with less than daily cannabis use, increase validity
At least once weekly Internet access and a valid email address	To ensure at least some access to the intervention
Good command of the German language	To ensure that participants will be able to understand the information provided

**Table 2 table2:** Exclusion criteria and underlying rationale.

Exclusion criteria	Reasoning
Participation in other psychosocial or pharmacological treatments for the reduction or cessation of cannabis use	To avoid confounding treatment effects
Current pharmacologically treated psychiatric disease or any history of psychosis, schizophrenia, bipolar type I disorder, or significant current suicidal or homicidal thoughts	To avoid having subjects with these problems enter the study

As participants assigned to TAU will immediately become aware of this, we expect that some might try to circumvent their assignment by registering another account, hoping to end up in a different group. If anyone attempts this, he or she nevertheless will be assigned to the original group when they try to register again on the same day based upon his or her Internet protocol address.

Participants will be introduced step by step into the corresponding study arm and, in the cases of study arms 1 and 2, be invited to participate in the program. Participants assigned to study arm 3 will be informed that they will be provided access to the Web-based self-help treatment after 3 months (with TAU until they are 3 months past their baseline assessment). Participants in study arms 1 and 2 will receive automated email notifications to log in and enter their cannabis consumption quantity and frequency into their consumption diary every week.

The two experimental interventions will each last 6 weeks. Follow-up assessments will be 6 weeks and 3 months after the start of the program. As such, there will be a baseline (pretreatment) assessment, a 6-week assessment immediately following the treatment program, and a final assessment 6 weeks posttreatment (3 months postbaseline).

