The control condition will be TAU. As these subjects will have access to any other online and offline drug counseling services that are available, they will be asked about their possible use of other treatment services over the course of observation at their final follow-up visit.

Follow-up assessments should be completed online after a reminder is sent by email, in which they also will be reminded that, upon completion of the entire 3-month follow up assessment, they will be compensated with 30 Euro (via either an Web-based voucher or the choice to make an online charitable donation). If the final assessment is not completed within 2 days, the same reminder will be sent out two more times, 2 days apart. If these reminders still go unanswered, participants will be contacted by phone within 1 week after the third email has been sent and offered an interview on the phone with study collaborators to complete the follow-up instruments. Should participants still refuse, they will be asked to answer questions about the primary outcomes only or—should they still refuse—to provide a reason for refusing, which will then be documented.

It is not uncommon for participants of Web-based interventions to take breaks, yet still complete the intervention later. Therefore, there are no dropout criteria relating to inactivity. The only dropout criterion is active withdrawal from the study by the participant, in which case only the data already gathered will be analyzed.

Figure 1 shows a flow chart depicting the flow of subjects through the study.

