### Hypotheses

We will test the following detailed study hypotheses with respect to the main outcome: reduction in the number of days of cannabis use over the past week, comparing the baseline, 6-week, and 3-month follow-up assessments:

An adherence-focused, guidance-enhanced, Web-based self-help program with a social presence (study arm 1) is more effective than an adherence-focused, guidance-enhanced, Web-based self-help program with no social presence (study arm 2) at reducing cannabis use.An adherence-focused, guidance-enhanced, Web-based self-help program to reduce cannabis use with a social presence (study arm 1) is more effective than TAU (study arm 3) at reducing cannabis use.An adherence-focused, guidance-enhanced, Web-based self-help program to reduce cannabis use without a social presence (study arm 2) is more effective than TAU (study arm 3) at reducing cannabis use.Participants in study arm 1 will demonstrate better adherence than participants in study arm 2 over the 6-week intervention.

We have similar expectations with respect to our secondary cannabis-related outcomes and will explore frequently co-occurring mental disorders as predictors of adherence and outcomes. Specifically, we also want to explore, for the first time, the influence of attention deficit hyperactivity disorder (ADHD) symptoms on adherence to and outcomes from a Web-based intervention among problematic cannabis users.

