#### Dashboard

The dashboard (see Figure 2) serves as the central hub, displaying useful information at a quick glance. On the dashboard, participants can see the date when they started the program and how many days remain for them in it. It also displays the dates of the two follow-up assessments and indicates when they have been completed. The same is true of the individual intervention modules, and by clicking a link, participants will be taken to the page in the module where they left off the last time they logged in. There is also a way for subjects to directly enter cannabis consumption data over the preceding week, which then displays a consumption graph.

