### Limitations

The following protocol limitations must be considered:

First, cannabis users who are currently receiving other treatments to reduce their cannabis consumption will be excluded. However, CANreduce was designed to access cannabis users who—for personal or practical reasons—would not attend traditional addiction counseling. Second, all measurements will be self-reported. Third, most of the self-report instruments we will be using have not been validated in a Web-based context, though they have largely been validated in other research and clinical settings. Fourth, as found in the previous Web-based intervention [10,22], we expect rather high rates of dropouts. Finally, another possible limitation of Web-based studies is the potential for low adherence rate because of the distant nature of intervention.

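### Repeat reminders and the phone follow-up are described only for the 3-month assessment, although the 6-week value belongs to the main-outcome hypotheses

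*Protocol article*

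**What the plan says.** Under Methods, Randomization and Trial Flow, the article sets out the assessment schedule and the reminders. The last assessment is defined as "a final assessment 6 weeks posttreatment (3 months postbaseline", separate from the one at 6 weeks. For both, the stated prompt is a single email: "Follow-up assessments should be completed online after a reminder is sent by email". The next step is limited to the last one: "If the final assessment is not completed within 2 days, the same reminder will be sent out two more times, 2 days apart". If those emails go unanswered, "participants will be contacted by phone within 1 week after the third email has been sent". The 30 Euro compensation is likewise tied to 3-month completion.

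The Hypotheses section states the main outcome as "comparing the baseline, 6-week, and 3-month follow-up assessments". Table 4 places the Client Satisfaction Questionnaire (CSQ-I) and the working alliance measure (WAI-TECH) at week 6 only.

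Other sections also bear on prompting:
- Registration and Consent Procedure says that the article collects "phone numbers (only to get in contact with if follow-up questionnaires are not filled out", with no restriction to the 3-month assessment.
- Dashboard, listed among the elements used in both active arms, says: "It also displays the dates of the two follow-up assessments and indicates when they have been completed".
- Automated Motivational Email Feedback gives arms 1 and 2 a weekly email with a diary reminder and a log-in link, and further diary reminders 1 and 3 days later if the diary is not filled in.
- Limitations states: "we expect rather high rates of dropouts".

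**The concern.** Week 6 is the end-of-treatment contrast and part of the main-outcome comparison, but the retention effort that is written down is concentrated on the 3-month assessment. A satisfaction or working alliance score missed at week 6 is not collected again. The working alliance measure captures the perceived relationship with the eCoach, which is close to the question that separates arm 1 from arm 2.

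The cues around week 6 also differ by arm. Participants in arms 1 and 2 see the follow-up dates and receive weekly emails. TAU participants know their allocation and wait 3 months for access, and no comparable cue is described for them. If prompting affects response, any shortfall could be largest in the comparator of hypotheses 2 and 3. The week-6 contrast with TAU would then rest more heavily on the imputation model.

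**Working it through.** **Step 1: which assessment the escalation belongs to.** The opening sentence on reminders is plural and covers both follow-ups with one email. The following sentence names the final assessment, which the same section fixes at 3 months after baseline. The phone call is timed from the third email, so it belongs to the same sequence. No sentence gives a second email for week 6.

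**Step 2: what is described at week 6, by arm.**

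| Cue | Arms 1 and 2 | TAU |
|---|---|---|
| One email reminder for the assessment | yes | yes |
| Dashboard with follow-up dates and completion status | yes | not described |
| Weekly email with log-in link | yes | not described |
| Two repeat emails, then phone | not described | not described |

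The weekly emails concern the diary and log-in, so they are indirect cues to the assessment.

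**Step 3: the consent section.** It gives the purpose of the phone numbers as follow-up questionnaires in general. This is wider than the trial-flow section, where the phone call comes only after the third email about the final assessment. The two texts leave open whether any phone contact is made at week 6.

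**Step 4: the plan's own figure, as background.** The inputs from Sample Size Calculation are d = 0.30, two-sided alpha 5%, 80% power and 176 per arm. With n = 2(1.96 + 0.84)² / d², the result is 175 per arm. The two-sample t-test gives 175.4, rounded up to 176, with power 80.1%. The stated 176 is reproduced. The recruitment target is 3 × 176 = 528, with no stated allowance for loss.

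**Step 5: what missingness costs in general.** Take power = Φ(d√(n/2) − 1.96), with n = 176(1 − m) and equal loss m in each arm. The loss rates are assumptions, and the analysis is complete-case at one time point.

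| Missing | n per arm | Power |
|---|---|---|
| 0% | 176 | 80.4% |
| 10% | 158.4 | 76.1% |
| 20% | 140.8 | 71.1% |
| 30% | 123.2 | 65.3% |
| 40% | 105.6 | 58.7% |
| 50% | 88 | 51.2% |

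This shows only that missing responses are not free. It does not measure the effect of reminders, and it ignores the mixed models and multiple imputation planned under Data Analyses, which recover part of the loss.

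**Step 6: what two more emails might do.** This needs an initial response r and a yield q per extra email, and the article gives neither. With assumed values, response = 1 − (1 − r)(1 − q)², and the complete-case standard error ratio is √(r/response):

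| r | q | Response | Fall in standard error |
|---|---|---|---|
| 0.4 | 0.1 | 51% | 12% |
| 0.4 | 0.3 | 71% | 25% |
| 0.6 | 0.1 | 68% | 6% |
| 0.6 | 0.3 | 80% | 14% |

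The spread comes entirely from the assumptions. It is not an estimate for this trial.

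**The case against.** The strongest reply is that the article is a condensed account and nowhere says that week-6 non-responders are left alone after one email. A reminder schedule for each time point could sit in the full protocol, and the consent section suggests that phone contact was not meant for 3 months only. This stands to the extent that a reader who infers that week 6 definitely gets one prompt and nothing more goes beyond the text. What remains is that the article does state a rule, restricts it to the final assessment, and does not match the wider wording in the consent section.

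A reader might also infer that week-6 non-response will be high and will differ by arm. The documents do not support that as a fact. They give no week-6 response rate, overall or by arm, and the expected high dropout under Limitations is tied neither to week 6 nor to reminders. The active arms have other cues at week 6, so a difference by arm is plausible, but its size and direction are unknown. A stated gain of 6 to 25% in the standard error would be equally unsupported, for the reasons in steps 5 and 6.

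Finally, concentrating effort on the last assessment limits burden and is a coherent choice. But two automated emails sent only to non-responders are a small burden. A change during recruitment would apply equally to concurrently randomised arms, so this is hardly a real trade-off.

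**Conclusion.** The point holds as a cheap improvement to the design and a request to reconcile two sections. The repeat emails, and the phone call that follows them, are written for the 3-month assessment only. The 6-week assessment serves the main-outcome hypotheses and is the sole source of the satisfaction and working alliance data. Week-6 missing data may be higher than necessary and may differ between TAU and the active arms. The size cannot be computed from the article.

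The conclusion assumes that the trial-flow section describes the operative procedure, and that repeat reminders would recover some responses. If the full protocol already applies the same sequence at week 6, only the inconsistency in wording remains.

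**What to change.** State in Randomization and Trial Flow that the same two automated email reminders, 2 days apart, are also sent for the 6-week assessment in all three arms. In the same edit, say whether phone contact applies at 6 weeks, so that this section agrees with Registration and Consent Procedure. Phone calls at week 6 and changes to compensation are not needed for this improvement. If the sequence already applies at week 6, one sentence saying so is enough.

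The cost is small. Automated emails already run in the system, including repeat diary reminders, so this is one more rule. Week-6 non-responders receive up to two extra emails. If enrolment is under way, a minor procedural amendment is needed, applied to all arms from the same date. The change does not remove the difference in dashboard and weekly emails between the active arms and TAU, so week-6 response should still be reported by arm.

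### The primary-outcome-only fallback is offered only inside the phone contact, so participants the call does not reach never get it; a short web page sent after the phone step would close the gap at little cost

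*Protocol article*

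**What the plan says.** The follow-up sequence is in the protocol article, Methods, Randomization and Trial Flow. It is written for the 3-month assessment: "If the final assessment is not completed within 2 days", then "the same reminder will be sent out two more times, 2 days apart". The next step is that "participants will be contacted by phone within 1 week after the third email has been sent and offered an interview on the phone". Members of the study team conduct this interview. After that: "Should participants still refuse, they will be asked to answer questions about the primary outcomes only". Anyone who still refuses is asked for a reason, which is documented. No emailed or online form of the short route is described, and no step follows for a person the call does not reach. The emails tell participants that "upon completion of the entire 3-month follow up assessment, they will be compensated with 30 Euro".

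Three other places bear on this:
- Registration and Consent Procedure: participants supply "phone numbers (only to get in contact with if follow-up questionnaires are not filled out").
- Sample Size Calculation: 176 per group for d = 0.30, 80% power, two-sided 5%, hence 528 in total. No dropout allowance is stated.
- Limitations: "we expect rather high rates of dropouts".

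**The concern.** The primary outcome is the number of days of use in the preceding 7 days, which is quick to answer. The full 3-month battery is long. Using the item counts in Measurements, the CES-D (20), CUDIT-R (8), GAD-7 (7), PTSD screen (7), ASRS (6) and SDS (5) alone come to 53 items, before substance history, quantity and frequency of use, negative effects and other treatments. As described, all three emails ask for the whole assessment, and the short request exists only as a spoken question late in a phone contact.

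The sponsor already accepts primary-outcome-only data, but one group of non-responders has no route to give it: those who do not pick up or who end the call. Each such person is a missing 3-month primary outcome in a trial whose sample size reaches its stated power only with complete data.

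**Working it through.** **1. Who is offered the short route, as the text stands**

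| Participant at 3 months | Offered primary outcomes only? |
|---|---|
| Completes after one of the three emails | Not needed |
| Reached by phone, accepts the interview | Not needed |
| Reached by phone, declines the interview | Yes |
| Not reached by phone, or ends the call | No |

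The gap is the last row only.

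**2. The plan's own figure**

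Inputs from Sample Size Calculation: d = 0.30, two-sided 5%, 80% power. For a two-sample t-test the noncentrality is d × √(n/2). Solving for 80% power gives n = 175.4, rounded up to 176 per arm; 3 × 176 = 528. At n = 176 the noncentrality is 0.30 × √88 = 2.81 and power is 80.1%. The figure reproduces, with every randomized participant contributing an outcome.

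**3. Illustration of what a written short route could add**

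The documents give no response rates. All of the following are assumptions: a share a = 40–60% does not answer the emails; the phone yields primary data from y = 30–50% of those; a short web page recovers r = 10–30% of those still missing.

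- Missing after the phone step = 176 × a × (1 − y)
- Observed n = 176 − missing
- Added n = r × missing

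| a, y | Missing per arm | Observed n | Power | Added n (r = 10%, 30%) | Power after | Gain in points |
|---|---|---|---|---|---|---|
| 40%, 50% | 35.2 | 140.8 | 70.8% | 3.5, 10.6 | 71.9%, 73.9% | 1.1, 3.1 |
| 60%, 30% | 73.9 | 102.1 | 56.9% | 7.4, 22.2 | 59.9%, 65.4% | 3.0, 8.5 |

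The other two combinations of a and y give gains between 1.7 and 5.3 points. The range is therefore roughly 1 to 8 points (8.5 at the extreme) on a t-test of observed cases.

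**4. Two limits on that range**

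Data Analyses plans multiple imputation using all primary and secondary outcomes, and mixed models over the repeated measures. Baseline and any 6-week data recover part of the information, so the real gain is smaller. Also, r is applied to everyone still missing, including people who were reached and already refused the short questions; the group that was never offered them is smaller.

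**The case against.** The case against is substantial, and most of it stands.

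- **The sequence is defensible.** Asking for everything first and shrinking the request on refusal protects the secondary outcomes, which also feed the imputation model. Three emails, a 30 Euro incentive, a phone interview, a short fallback and a recorded reason make a serious retention effort. A reader might infer that the order is wrong or self-contradictory; nothing in the article shows that.
- **Replacing a full reminder with the short page would cost data.** Some who would have completed everything might stop there. This is why the short page belongs after the phone step.
- **Unwillingness to talk is mostly covered.** A reader might infer that anyone who declines to discuss drug use by phone loses the short route. The text says the opposite for those who are reached and decline.
- **Anonymity does not conflict with the call.** It is tempting to set "anonymity is ensured by not recording real names or postal addresses" against a phone call. But that sentence goes on to say that emails and phone numbers are deleted before analysis, and participants give their number for exactly this purpose. That they would avoid the call on these grounds is conjecture.
- **Bias from mixing spoken and web answers is speculative and small.** If phone shares differed by 10 points between arms and spoken answers ran 0.5–1.0 day lower (both assumed), the bias would be 0.10 × 0.5 = 0.05 to 0.10 × 1.0 = 0.10 day. With an assumed SD of 2.2–2.5 that is d = 0.02 to 0.045, or 7–15% of 0.30. It would concern every phone answer, not the position of the short route.
- **Recovery is unsupported.** People who ignored three emails may ignore a fourth.
- **The article is a condensation.** A short online form may exist in the full protocol. However, the article gives the order, spacing and repetition of the steps explicitly, so its description can be taken as the intended procedure.

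**Conclusion.** The point holds in a narrow form. As described, the primary-outcome-only route is available only to participants reached by phone who decline the full interview; those not reached, or who end the call, are never offered it. With high dropout expected and no allowance in the 176 per arm, some 3-month primary outcomes may be lost that a short written request could have obtained.

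The size cannot be derived from the documents. The range of roughly 1 to 8 points rests on assumed non-response, phone yield and recovery and on observed-case tests, and it overstates the gain to the extent that imputation and 6-week data help. The low end is three to four people per arm. A reader might attribute the illustrated 57–71% power to this sequence. That shortfall comes from the assumed dropout set against a sample size with no margin, which is a separate matter; only the increment belongs here.

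This is an optional, low-cost improvement, not an error or contradiction.

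**What to change.** Keep the three full reminders and the phone step as they are. Then, identically in all three arms:

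1. Send one further email to everyone whose 3-month primary outcome is still missing and who has not withdrawn. It links to a single self-completed page with the 7-day Time-Line-Follow-Back question, saved on submission, with a button to continue to the full assessment.
2. State in that email that the compensation condition, completion of the entire 3-month assessment, is unchanged.
3. Store the collection mode (web full, web short, phone) and the date of the answer, so that the primary contrast can be checked by mode.

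The cost is one web page, one email and two stored fields, with no extra staff and no full prompt given up.

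The main drawback is timing. Reminders at days 0, 2 and 4 and a call within 7 days of the third put the end of the phone step at about day 11, so short-page answers come slightly later than planned. TAU participants are offered the program after 3 months, so the stored date also shows whether a late answer could follow that access. The email must go out before contact details are deleted.

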The short screening scale for DSM-IV PTSD is designed to assess for a lifetime history of PTSD [43]. A score of 4 or more on the seven-symptom screening scale suggests PTSD.

The CSQ-I has been shown to be a suitable measure from the user’s perspective in the evaluation of Web-based health interventions. It is scored easily by summing up the individual item scores to produce a score ranging from 8 to 32, with higher scores indicating greater satisfaction [44].

Furthermore, the occurrence of any negative effects will be identified, as in Rozental et al, at the 3-month follow-up assessment [45].

Finally, we will ask all participants if they had used any other treatment than canreduce.ch during the 3 months and if so, to select from a predefined list of services.

As an indicator of treatment adherence, data will be collected on which modules have been completed by the participant and the number of weeks the consumption diary was filled out. Additionally, a script has been implemented that allows us to measure the time that subjects spend on each page. To avoid false data that might result if a participant leaves a Web page open but switches to a different window or leaves the computer, a cutoff time of 10 min inactivity has been set, after which the time spent on the page is disregarded and not saved to the database. These data could potentially lead to insights into how and specifically where to optimize CANreduce to further decrease attrition rates. We also will assess the number of individual emails received by each participant.

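### Negative effects are asked only at 3 months and are left out of the fallback interview, so reduced-interview responders and early withdrawers have no record of them

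*Protocol article*

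**What the plan says.** Under Measurements, the article states that "the occurrence of any negative effects will be identified" at the 3-month follow-up. Table 4 agrees: this item has one mark, in the 3-month column, and none at week 6.

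Randomization and Trial Flow sets the path for people who do not complete the final assessment. After three emails they are phoned and "offered an interview on the phone with study collaborators to complete the follow-up instruments". If they decline, "they will be asked to answer questions about the primary outcomes only". Only those who refuse this as well are asked "to provide a reason for refusing, which will then be documented".

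The same section deals with leaving. For users who merely stop using the tool, "there are no dropout criteria relating to inactivity". For the rest: "The only dropout criterion is active withdrawal from the study by the participant, in which case only the data already gathered will be analyzed". Under Limitations the authors write that "we expect rather high rates of dropouts", without giving a figure.

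**The concern.** An item that is measured once, at the last visit, is lost whenever that visit is lost or shortened. Here the shortening is a stated rule: the reduced interview keeps the primary outcome and drops everything else. A participant who accepts it ends the trial with no answer on negative effects and no recorded reason for declining the rest. A participant who withdraws earlier has nothing on negative effects among the data already gathered.

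The negative-effects rate for each arm would then describe full-questionnaire completers. If having a negative effect makes someone more likely to decline the long interview or to withdraw, that rate is too low. Even if it does not, the rate comes from fewer people. The loss cannot be repaired later, because Technical Specifications has email addresses and phone numbers deleted once a participant's time in the study is over.

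**Working it through.** **Step 1: trace each path to the negative-effects item.** Sources: Randomization and Trial Flow, Measurements, Table 4.

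| Path at 3 months | Negative-effects item | Reason asked |
|---|---|---|
| Completes online | Collected | Not applicable |
| Ignores emails, accepts full phone interview | Collected | Not applicable |
| Declines full interview, accepts reduced one | Offered within the full set, then dropped | No |
| Declines both | Offered, then dropped | Yes |
| Cannot be reached by phone | Not collected | No |
| Stops using the tool, does not withdraw | Stays in follow-up; falls into one of the rows above | As above |
| Withdraws before 3 months | Not reached | None described |

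The fallback and withdrawal rules leave two groups without a record: row 3 and the last row.

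**Step 2: look for something else in the article that fills the gap.**
- Safety expects craving, mild depressive states and sleep problems. It describes a help page but no data collection.
- The depression and anxiety scales are scheduled at baseline and 3 months only (Table 4), so they are lost together with the negative-effects item.
- The imputation model in Data Analyses covers primary and secondary outcomes. Negative effects are not in the list of secondary outcomes under Measurements. Leaving a descriptive harm item unimputed is no error; it only means that this model does not cover it.
- Results promises annual safety reports to the ethics committee and authorities but does not say what feeds them.

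**Step 3: size, under assumptions.** The article gives no negative-effects rate to reproduce. The only input taken from it is the arm size. With d = 0.30, two-sided alpha 5% and 80% power, the t-test calculation gives 175.4, rounded up to 176 per arm, and 3 × 176 = 528, as stated under Sample Size Calculation.

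Let m be the share of an arm without the item, p the rate among those who answer, and r the ratio of the rate in the missing to the rate in the answering. Then

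true rate = (1 − m)·p + m·r·p = p·[1 + m(r − 1)].

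All values of m, p and r are assumptions. With p = 10%:

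| m | Answering, of 176 | r = 1 | r = 2 | r = 3 | 95% upper bound if no event is seen |
|---|---|---|---|---|---|
| 0% | 176 | 10% | 10% | 10% | 1.7% |
| 20% | 141 | 10% | 12% | 14% | 2.1% |
| 40% | 106 | 10% | 14% | 18% | 2.8% |
| 60% | 70 | 10% | 16% | 22% | 4.2% |

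The last column is 1 − 0.05^(1/k), with k the number answering. For m = 40% and r = 3: 10% × (1 + 0.4 × 2) = 18%. With p = 5% and r = 3, the true rates are 7%, 9% and 11% for m = 20%, 40% and 60%.

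**Step 4: the part that belongs to these two rules.** m counts everyone without the item, including people who cannot be reached and people who refuse everything. If s is the share in the two affected groups alone, their contribution to the bias is s·(r − 1)·p. For s = 10% (about 18 of 176), p = 10% and r = 3, that is 0.10 × 2 × 10% = 2 percentage points. At r = 1 it is zero.

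**The case against.** The strongest reply is that the plan tries hard to get the full instrument: three emails, a phone offer of the complete set, and 30 Euro for finishing the 3-month assessment. Cutting the fallback to the primary outcome is a deliberate trade to protect that outcome among reluctant respondents. Safety reporting outside this questionnaire is promised, and a condensed article need not describe it. All of this stands. It limits how many people are affected and how much weight the point can bear, but it does not give the two groups a record.

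A reader might infer several stronger things that the documents do not support:

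- *That people who left because of negative effects are never asked about them.* Non-responders who have not withdrawn are offered the full instruments first. Inactive users stay in follow-up. People who refuse everything are asked why, and the answer could reveal a harm.
- *That dropout is driven by negative effects.* The article does not say so. The reasons for stopping the tool given under Automated Motivational Email Feedback are favourable: a modest goal met early, or early abstinence.
- *That the whole bias in the table comes from the fallback rule.* Most of m may be people whom no change to that rule would reach.
- *That the trial's safety conclusion, or a comparison of harms between arms, rests on this item alone.* The article plans no such comparison under Hypotheses or Data Analyses, and it does not describe the basis of the safety reports.

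**Conclusion.** The point holds in limited form. As written, reduced-interview responders and participants who withdraw before 3 months have no negative-effects record, and the former are not asked for a reason. The rate therefore rests on full-questionnaire completers.

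The loss of precision is certain in direction, but its size depends on the share missing. At an assumed 40% missing, the upper bound with no events seen rises from 1.7% to 2.8% per arm. Bias is possible, not shown. It is zero if the rates are equal, and with the assumed 10% rate among those who answer it is about 2 percentage points for each 10% of an arm in the two affected groups if their rate is three times as high. The article gives neither rate, so no figure can be put on the actual bias.

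The primary analysis is unaffected. Whether the full protocol records adverse events at withdrawal cannot be judged from this article. This is a cheap improvement to a stated rule, not an error that invalidates anything.

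**What to change.** In Randomization and Trial Flow, extend the fallback interview to the primary outcome followed by one optional global question on negative effects since baseline (none, or yes with free text). Ask it second, so that the primary answer is already secured. Offer the same optional question when a participant withdraws, clearly as voluntary. Report these answers by arm, separately from the full instrument because they are less detailed, and give the number not asked and the number not answering.

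The cost is one line in an existing call script, one optional field at withdrawal, and a few seconds for a reluctant respondent. The change does not reach people who cannot be contacted or who refuse everything, so the count of those without an answer still has to be shown. If the full protocol already records negative effects at withdrawal, a sentence saying so would settle that half of the point.
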